## Abstract

**Background:**

Tubal ectopic pregnancy is a life-threatening condition in early pregnancy. Minimally invasive laparoscopic surgery is increasingly used for the treatment of this disease. Retrospective studies suggest that Transvaginal Natural Orifice Transluminal Endoscopic Surgery (vNOTES) offers lower perioperative complications, faster recovery, and better cosmetic outcomes compared to other approaches. However, the lack of comprehensive perioperative and long-term postoperative data limits its widespread adoption in gynecology.

**Methods:**

The vNOTESTEP study is a randomized controlled trial (RCT) enrolling 72 patients requiring laparoendoscopic surgery for tubal ectopic pregnancy. After obtaining informed consent, preoperative assessments will be conducted. Following randomization, salpingectomy will be performed using either vNOTES or TU-LESS approach. The postoperative assessment and a structured 5-year follow-up, including eight visits, will be conducted. Baseline sociodemographic and clinical data will be collected from the Hospital Information System and patient interviews. Outcomes will be assessed perioperatively and postoperatively at designated time points (1st, 2nd, and 3rd postoperative day; 1st, 3rd, and 6th month; 1st–5th year). Key long-term outcomes include sexual function, pregnancy, vaginal delivery, and incisional hernia.

**Discussion:**

This RCT aims to provide robust clinical evidence on the perioperative and long-term outcomes of vNOTES versus TU-LESS for tubal ectopic pregnancy, focusing on key reproductive and surgical outcomes. The study seeks to refine patient selection criteria and contribute to guideline development for gynecologic vNOTES.

**Trial registration number:**

ChiCTR2400082909 (registered on April 10th, 2024).

**Supplementary Information:**

The online version contains supplementary material available at 10.1186/s12884-025-07595-z.

## Background

Ectopic pregnancy occurs when an embryo implants outside the uterine cavity, most commonly in the fallopian tubes [1]. It accounts for approximately 3% of all pregnancies and 10% of maternal morbidity, posing a significant threat to maternal health. Surgical intervention remains the primary treatment, with laparoscopy being the preferred approach due to its minimally invasive nature [2]. 

Efforts to minimize surgical trauma have driven advancements in minimally invasive surgery (MIS) [3, 4]. Among various MIS approaches, Natural Orifice Transluminal Endoscopic Surgery (NOTES) represents an innovative yet debated technique [3–6]. NOTES utilizes natural orifices (e.g., mouth, rectum, urethra, vagina) to perform endoscopic procedures without visible abdominal scars.11 Its feasibility was first demonstrated in 2003 with a transgastric appendectomy [7]. Since then, NOTES has been applied in cholecystectomy [8], gastrostomy [9], nephrectomy [10], oophorectomy [11], and ovarian cystectomy [12, 13]. Its advantages include reduced postoperative pain, minimal hemorrhage, and improved cosmesis [14, 15]. However, concerns regarding limited operative space, difficult suturing, and steep learning curves remain [16]. 

Transvaginal NOTES (vNOTES) mitigates some challenges associated with other NOTES approaches and is increasingly preferred in gynecology [17–19]. The vaginal route offers favorable anatomical characteristics, including good ductility, strong healing ability, ample operative space, and proximity to target organs [16, 20]. Since Zorron et al. first performed transvaginal endoscopic cholecystectomy [21], vNOTES has been applied to a range of benign gynecologic conditions [20, 22–25]. It has even been explored in the treatment of early-stage gynecologic malignancies [26]. A previous study on hysterectomy and bilateral adnexectomy in transgender men also demonstrated that vNOTES is a feasible and safe alternative to laparoscopic surgery [27]. 

Despite its potential, concerns remain regarding vNOTES’ impact on sexual function, pregnancy, vaginal delivery, adjacent organ damage, and incisional complications [14, 15]. Several retrospective studies have assessed vNOTES’ safety and effectiveness, though the lack of RCTs introduces potential bias [14, 20, 28–31]. Existing RCTs, such as the HALON and NOTABLE studies [23, 24, 32, 33], focus on hysterectomy and adnexectomy, leaving gaps in evidence for tubal ectopic pregnancy.

Our institution has extensive experience with vNOTES, performing 500–600 cases annually, alongside 1000–2000 TU-LESS procedures. Retrospective studies suggest vNOTES has lower perioperative complication rates but slightly higher conversion rates than TU-LESS [25, 34]. Given the similarities and controversies between these approaches, we designed the vNOTESTEP study to systematically evaluate vNOTES’ feasibility, safety, and long-term outcomes in treating tubal ectopic pregnancy.

## Methods

### Study design

The vNOTESTEP study is a single-blind RCT designed to evaluate the perioperative and long-term postoperative outcomes of vNOTES compared withTU-LESS in patients with tubal ectopic pregnancy. Considering ethical concerns and the low likelihood that patients would be unaware of their incision site, this study will adopt a single-blind design, with blinding applied only to the outcome assessors (OAs) and not to the patients. After obtaining informed consent from each participant, preoperative assessments will be conducted. Following randomization, salpingectomy will be performed via either vNOTES or TU-LESS approach. The primary outcomes include perioperative outcomes like surgical conversion, change of postoperative sexual function, pregnancy, and vaginal delivery. The study will be conducted at CWCCH, a university teaching hospital and regional training center for vNOTES, spanning from 2024 to 2030, with two years allocated for recruitment and three to five years for follow-up.

CWCCH has a highly experienced team of approximately 20 gynecologic endoscopic specialists, who collectively perform 500–600 vNOTES and 1000–2000 TU-LESS procedures annually. Randomization and grouping will be performed by a cohort manager (CM) using a computer-generated system after stratification. To maintain blinding, identifiable patient information will be removed. Outcome assessors (OAs) will be blinded to patient allocation, with OA1 responsible for evaluating incisional wounds and OA2 assessing non-incisional wound-related perioperative and postoperative outcomes. Both the umbilical and vaginal incisional sites will be dressed uniformly to achieve blinding during hospitalization. Patients will not be informed of the type of surgery they undergo either preoperatively or postoperatively to maintain blinding as much as possible. In cases of severe incisional complications, blinding may be lifted for appropriate medical intervention. Information exchange between CM, OAs, and cohort coordinators (CCs) will be restricted until the study’s completion.

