### Study population

#### Sample size calculation

Sample size estimation was based on the NOTABLE cohort study [24]. Previous studies report a conversion rate for vNOTES in tubal ectopic pregnancies between 1.83% and 3.07%, suggesting a surgical success rate of approximately 95%.^34,35^A one-sided non-inferiority test was used to determine the sample size, assuming that vNOTES would remain a preferred option despite a potential 15% lower success rate compared to TU-LESS, which results in visible scarring. To achieve 85% power for non-inferiority with a 95% expected success rate in both groups, a total of 54 cases were required. Accounting for an anticipated 20% dropout rate, the final sample size was set at 72 participants, with 36 per group.

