**Body Image Questionnaire (BIQ)**: An eight-item scale assessing postoperative body image and cosmetic perception. Items 1–5 evaluate patients’ self-perception and satisfaction with their appearance, while items 6–8 assess satisfaction with the surgical scar [36, 37]. BIQ will be administered at the 1-month follow-up visit.**Visual Analog Scale (VAS)**: A validated tool for pain assessment, consisting of a 10 cm-long scale ranging from ‘no pain’ to ‘extreme pain.’ Patients will indicate pain intensity on postoperative days 1, 2, and 3. Pain scores will be classified as: <1 cm (painless), 1–3 cm (mild), 4–6 cm (moderate), and 7–10 cm (severe). CCs will record and upload VAS scores to the study database.**Female Sexual Function Index (FSFI)**: A validated 19-item scale assessing six domains of sexual function, including libido, arousal, lubrication, orgasm, satisfaction, and pain [38]. A total score < 26.5 indicates impaired sexual function [39]. The FSFI will be administered preoperatively and postoperatively at 3 and 6 months. Since sexual activity is contraindicated for one month following vNOTES to allow vaginal incision healing, FSFI will not be assessed at earlier time points [40]. **Pregnancy and delivery outcomes**: A self-designed **Pregnancy and Delivery Questionnaire (PDQ)** collecting postoperative gestational history (see Appendix 1). The PDQ includes seven questions regarding pregnancy status, conception method, delivery mode, parity, vaginal laceration, and incisional hernia (IH). This will be administered at all follow-up visits except the 1st month. Patients will be encouraged to undergo pregnancy monitoring and delivery at CWCCH to facilitate comprehensive data collection via HIS.**Incisional complications**: At each follow-up visit, patients will undergo gynecologic physical examinations to assess for IH. Patients with suspected IH (i.e., those experiencing incisional pain or a bulge) will be referred for imaging investigations, including ultrasound, computed tomography (CT), or magnetic resonance imaging (MRI). Diagnosed IH cases will be treated appropriately, and CCs will document relevant findings in the study database.

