### Perioperative assessment and short-term postoperative outcomes

#### Primary short-term outcome

Completion of surgery using the allocated technique is Primary short-term outcome that we will focus on. We will also conduct a detailed analysis of cases requiring surgical conversion, including the reasons for conversion, the type of surgical techniques converted into, as well as the specific complications and their severity.

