### Long-term postoperative outcomes

#### Primary long-term outcomes

Pregnancy and vaginal delivery outcomes and incidence of incisional wound complications.

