#### Secondary long-term outcomes

Cosmetic satisfaction, impact on sexual function, pregnancy outcomes, and IH occurrence. These outcomes will be evaluated according to the follow-up schedule outlined in Figs. 1 and 2.

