### Statistical analysis

Statistical analyses will be conducted using SPSS (Version 25.0) and R. Continuous variables will be analyzed using t-tests or Mann–Whitney tests, with results presented as means ± standard deviations for normally distributed data and medians with interquartile ranges for non-normally distributed data. Categorical variables will be analyzed using chi-square or Fisher’s exact tests. To mitigate bias, statistical techniques such as propensity score matching (PSM), stratification, multivariate analysis, Cox regression, and generalized estimating equations (GEE) will be employed as necessary. A binary logistic regression analysis will also be conducted to assess the risk factors for surgical conversion, incorporating variables that demonstrate a significant statistical difference in the univariate comparisons. Statistical significance will be set at *p* < 0.05.

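### The sections name different primary outcomes, and some outcomes are both primary and secondary, so the article does not fix which outcome decides the trial

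*Protocol article*

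**What the plan says.** Four places in the Methods of the protocol article assign outcome labels.

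- Study design: "The primary outcomes include perioperative outcomes like surgical conversion, change of postoperative sexual function, pregnancy, and vaginal delivery".
- Primary short-term outcome: "Completion of surgery using the allocated technique is Primary short-term outcome that we will focus on".
- Primary long-term outcomes: "Pregnancy and vaginal delivery outcomes and incidence of incisional wound complications".
- By contrast, the section headed Secondary long-term outcomes lists: "Cosmetic satisfaction, impact on sexual function, pregnancy outcomes, and IH occurrence".

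Three other statements bear on the point.

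- Items of follow-up visits describes the incisional complications item as an examination for hernia: "At each follow-up visit, patients will undergo gynecologic physical examinations to assess for IH".
- Sample size calculation concerns surgical success only, where a "one-sided non-inferiority test was used to determine the sample size".
- Statistical analysis closes with one line on error control: "Statistical significance will be set at *p* < 0.05".

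**The concern.** A published protocol should settle, before results are known, which outcome carries the trial's conclusion. Here that depends on which section is read. Sexual function is primary in one place and secondary in another. Pregnancy is primary in two places and secondary in a third. Incisional complications are primary in one list and absent from the other, and their main follow-up component, hernia, is secondary.

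A later report could present any of these outcomes as primary and cite a section in support. Readers could not tell a planned primary result from one chosen after the data were seen. The long-term outcomes also have no sample-size calculation, so the primary label promises more than the trial was sized to give.

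**Working it through.** **1. The lists side by side**

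| Outcome | Study design | Primary short-term / long-term sections | Secondary long-term section | In the sample size? |
|---|---|---|---|---|
| Conversion / completion | primary | primary (short-term) | – | yes |
| Sexual function | primary | – | secondary | no |
| Pregnancy | primary | primary (long-term) | secondary | no |
| Vaginal delivery | primary | primary (long-term) | – | no |
| Incisional complications | – | primary (long-term) | hernia: secondary | no |

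Study design names four. The short-term and long-term sections together also name four. Three are common to both (completion is the complement of conversion), so the union is 4 + 4 − 3 = 5. Sexual function and pregnancy are plainly both primary and secondary. Hernia overlaps with a primary outcome. Splitting primaries into short-term and long-term does not remove either of the first two conflicts.

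**2. What was sized**

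The plan's inputs are 95% success in both arms, a 15-point margin, 85% power, and 54 evaluable patients raised to 72 (36 per arm). The one-sided alpha is not stated. With unpooled variance, n per arm = 2 × 0.95 × 0.05 × (z₁₋α + z₀.₈₅)² / 0.15². This gives 31 per arm (62 in total) at one-sided 0.05, and 38 per arm (76) at 0.025. The stated 54 matches 80% power at one-sided 0.05, not 85%. That is a separate matter. What counts here is that only one outcome has any calculation.

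**3. Family-wise error if the candidates were each tested at 5%**

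For k independent tests of exact size 0.05 with every null true, the error is 1 − 0.95^k.

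- k = 4: 1 − 0.95⁴ = 18.5%.
- k = 5: 1 − 0.95⁵ = 22.6%.

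Fisher's test is conservative at this sample size. Enumerating the two-sided test at 36 per arm gives a true size of 0.3% at a 5% event rate, 0.7% at 7%, and 2.5–2.8% at 30–50%. Take conversion at 5%, incisional complications represented by hernia at 7%, pregnancy and vaginal delivery at 30–50% (assumed, because the article gives no rates), and sexual function at a full 5%:

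1 − 0.95 × 0.997 × 0.993 × 0.972 × 0.972 = 11.1% (10.6% with 0.975 for the last two).

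Most of this comes from sexual function. Without it, the four outcomes in the short-term and long-term primary sections give 1 − 0.997 × 0.993 × 0.972 × 0.972 = 6.5%. If completion is counted as a non-inferiority test at a nominal 2.5–5% instead of a Fisher test, the five-outcome figure is 1 − 0.95 × 0.975 × 0.993 × 0.972² = 13.1% to 1 − 0.95 × 0.95 × 0.993 × 0.972² = 15.3%.

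**4. Hernia as an example of a long-term outcome**

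The Discussion gives 5–7% hernia after TU-LESS. Take the most favourable contrast, 7% against 0%, with 36 per arm. Fisher's p-value is 0.054 for 5 v 0 and 0.025 for 6 v 0, so at least six events are needed. P(X ≥ 6 | n = 36, 0.07) = 3.7%. At 5% the power is 0.8%. With 27 per arm and 7%, it is 1.0%.

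**The case against.** The label conflict itself is hard to contest. The objections concern what is built on it.

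- *A reader might infer that the plan commits to five confirmatory tests, each at 5%, with a 23% error.* The article does not say so. It has one generic significance line, and an analysis plan that is not shown may set an order or an alpha split. The lack of a multiplicity rule here is therefore not a finding. Five is also the union of two conflicting lists, and either list alone gives four. Vaginal delivery requires pregnancy, so independence fails, and Fisher's test does not spend its full 5%. All of this stands, which is why 19–23% is only an upper illustration.
- *The sized outcome is a non-inferiority comparison*, so it is not simply one of several difference tests. This also stands.
- *A reader might take the hernia power as proof that the incisional primary outcome is hopeless.* Hernia is only one component. Incisional complications may be wider, and no rate for them is given. The Discussion already concedes that the sample may be too small for rare complications. That concession does not reconcile the lists.
- *A single primary outcome is a preference.* The abstract and the conclusion put sexual function, pregnancy, vaginal delivery and hernia at the centre, so a short-term primary with an ordered long-term set would also be coherent. This is fair: the error calls for consistent lists, and a sole primary is one way to get them.

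Nothing in the article shows an intention to choose among outcomes. The risk lies in the wording.

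**Conclusion.** The point holds as an internal contradiction. Study design, the two primary-outcome sections and the secondary long-term section cannot all be followed, and the outcome that decides the trial is not fixed. This rests on the shown text alone, and an unseen analysis plan would not remove it from the published article.

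The effect on error is secondary and depends on assumptions. If all five outcomes were tested separately at p < 0.05 with all nulls true, the family-wise error would be above 5%: about 11% when the binary outcomes use Fisher's test, and at most 19–23% for four or five independent tests of exact size. If sexual function were not among the primaries, the Fisher-based figure would be only about 6%, and the dependence of vaginal delivery on pregnancy would lower it further. The documents do not support 23% as the trial's actual error rate.

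**What to change.** Use one identical list in Study design, Primary short-term outcome, Primary long-term outcomes and Secondary long-term outcomes.

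- **Primary:** completion of surgery with the allocated technique, the only sized outcome, worded the same way each time (not conversion in one place and completion in another).
- **Secondary, each listed once:** sexual function, pregnancy, vaginal delivery, and incisional complications including hernia. Report these as estimates with 95% confidence intervals and no confirmatory claim.
- **If a long-term outcome is to stay primary:** state a fixed testing order or an alpha split. An order that starts with completion takes no alpha from it. An equal split is costly: with five outcomes at one-sided 0.05/5 = 0.01, the formula in step 2 of the working needs 96 evaluable patients for 85% power, and 54 would give about 58%.
- **Discussion:** extend the caveat on rare complications to hernia by name (about 4% power by Fisher for 7% v 0% at 36 per arm).

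The cost is wording in the article, plus a check that the registry record, which is not shown here, agrees. No patients, visits or data are added. The downside is that the long-term outcomes lose the primary label. The change should be made before outcomes are compared between arms.

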### Study population

#### Sample size calculation

Sample size estimation was based on the NOTABLE cohort study [24]. Previous studies report a conversion rate for vNOTES in tubal ectopic pregnancies between 1.83% and 3.07%, suggesting a surgical success rate of approximately 95%.^34,35^A one-sided non-inferiority test was used to determine the sample size, assuming that vNOTES would remain a preferred option despite a potential 15% lower success rate compared to TU-LESS, which results in visible scarring. To achieve 85% power for non-inferiority with a 95% expected success rate in both groups, a total of 54 cases were required. Accounting for an anticipated 20% dropout rate, the final sample size was set at 72 participants, with 36 per group.

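### The sample size names a one-sided non-inferiority test without an alpha, and its stated 85% power with 54 patients is not reached at one-sided 5% or 2.5%

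*Protocol article*

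**What the plan says.** The Sample size calculation section states that "A one-sided non-inferiority test was used to determine the sample size". It accepts a success rate for vNOTES up to 15% below that of TU-LESS and continues: "To achieve 85% power for non-inferiority with a 95% expected success rate in both groups, a total of 54 cases were required". It then allows for 20% dropout and sets 72 participants, 36 per group. No alpha is given.

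The Statistical analysis section says "Categorical variables will be analyzed using chi-square or Fisher’s exact tests" and closes with "Statistical significance will be set at *p* < 0.05". It does not say whether that threshold is one-sided or two-sided, and it does not mention the non-inferiority comparison. The outcome concerned is completion of surgery with the allocated technique, the primary short-term outcome.

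**The concern.** A non-inferiority conclusion depends on the margin and on the level at which the confidence limit is set against it. The article fixes the margin but not the level. Two readings are possible:

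- One-sided 5%, judged by the lower limit of a 90% confidence interval.
- One-sided 2.5%, judged by the lower limit of a 95% confidence interval. This is how a two-sided p < 0.05 would carry over.

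The sample size would normally show which was meant, but at the stated power it matches neither. This is the only comparison for which the article gives a power calculation. Few conversions are expected (36 × 0.05 = 1.8 per arm), so a single event can separate the two readings.

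**Working it through.** **Inputs from the Sample size calculation section.** Success 95% in both arms; margin 15%, read as absolute percentage points; power 85%; 54 evaluable (27 per arm); 72 randomised (36 per arm). Alpha is not stated, so one-sided 5% and 2.5% are assumed in turn.

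**Required size.** With the unpooled normal approximation,

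n per arm = 2 × 0.95 × 0.05 × (z_alpha + z_power)² / 0.15² = 4.222 × (z_alpha + z_power)²

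| One-sided alpha | Power | n per arm | Total |
|---|---|---|---|
| 5% | 85% | 4.222 × (1.645 + 1.036)² = 30.4, so 31 | 62 |
| 2.5% | 85% | 4.222 × (1.960 + 1.036)² = 37.9, so 38 | 76 |
| 5% | 80% | 4.222 × (1.645 + 0.842)² = 26.1, so 27 | **54** |

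The plan's 54 is reproduced in the last row only, at a power that is not the stated one. At the stated 85% power, three variants tried at these two levels all need more than 54: Farrington-Manning (90 and 114), a continuity correction (86 and 102), and a relative margin of 0.15 × 95 = 14.25 points (68 and 86).

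**Power actually delivered.** Power = Phi(0.15 / sqrt(0.095 / n) − z_alpha).

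- n = 27 per arm: 0.15 / sqrt(0.095 / 27) = 2.529. Power is Phi(0.884) = 81% at 5% and Phi(0.569) = 72% at 2.5%.
- n = 36 per arm: 0.15 / sqrt(0.095 / 36) = 2.920. Power is Phi(1.275) = 90% at 5% and Phi(0.960) = 83% at 2.5%.
- The one-sided alpha that would give 85% power with 27 per arm is 1 − Phi(2.529 − 1.036) = 0.068.

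The final 72 does not identify the alpha either. After 20% loss (72 × 0.8 = 57.6 evaluable), power at 5% is 83.3%. With no loss, power at 2.5% is 83.1%.

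**Effect on the verdict.** Lower limits for vNOTES minus TU-LESS with 36 per arm, in percentage points, against −15:

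| Completed, vNOTES vs TU-LESS | Method | 90% CI | 95% CI |
|---|---|---|---|
| 34/36 vs 35/36 | Newcombe | −12.9 (passes) | −15.6 (fails) |
| 34/36 vs 35/36 | Wald | −10.5 (passes) | −12.0 (passes) |
| 33/36 vs 35/36 | Wald | −14.4 (passes) | −16.1 (fails) |

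**How often the two levels disagree.** Summing exact binomial probabilities over all possible tables with 36 per arm:

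| True success, both arms | Method | Power, one-sided 5% | Power, one-sided 2.5% | Verdicts differ |
|---|---|---|---|---|
| 95% | Wald | 89.0% | 82.9% | 6.1% |
| 95% | Newcombe | 78.6% | 65.3% | 13.3% |
| 97% | Wald | 95.6% | 92.8% | 2.8% |
| 97% | Newcombe | 86.1% | 77.2% | 8.9% |

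The 97% rows are included because the section itself reports a "conversion rate for vNOTES in tubal ectopic pregnancies between 1.83% and 3.07" per cent, which implies success of 96.9% to 98.2%.

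**The case against.** The strongest reply is that the article can be read without ambiguity. One-sided in one section and 0.05 in the other combine to one-sided 5%. The 2.5% reading needs the general threshold to be two-sided and also to govern the non-inferiority test, and neither section says so. The match of 54 with one-sided 5% and 80% power supports this. These points stand, and the documents lean towards 5%. A reader might infer from the misfit that no conventional alpha was used. The documents do not support that, because the misfit points to the power figure at least as much as to alpha. Even so, reaching one-sided 5% means overruling a stated input, and the stated power would still be wrong.

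A second reply concerns size. A reader might take 13%, or about 16% with 29 per arm after 20% dropout, as the typical chance of a split verdict. That is too strong. Completion of the allocated technique is known when surgery ends, so later loss to follow-up barely affects it. The 13% is also the Newcombe figure at 95% success; Wald limits and higher success rates give less. For a given TU-LESS count from 0 to 3, the two levels differ by at most one allowed vNOTES conversion.

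Third, the interval method matters more than alpha. At the 95% level and 95% success with 36 per arm, power is 83% with Wald and 65% with Newcombe, a gap of 18 points against 6 to 13 for alpha. This stands, so naming alpha alone would not settle the decision rule.

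Finally, the full protocol or an analysis plan may name the alpha and the decision rule. That limits how serious the gap is, and nothing in the article suggests an intention to choose the level after seeing the data. It does not rescue the printed sample size statement, which is inconsistent with its own figures at either usual level.

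**Conclusion.** The point holds in a limited form. The non-inferiority test has no stated alpha, the only threshold has no sidedness and is not tied to it, and 85% power with 54 patients is not delivered at one-sided 5% or 2.5%. The shortfall in power is about 4 points (85 − 81) or 13 points (85 − 72). The source of the error cannot be identified from the article; a power figure that should read 80% is a plausible explanation but not a proven one.

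The choice of level would change the verdict in a minority of trials: about 6% to 13% at 95% success and 3% to 9% at 97%, depending on the interval method. These figures assume an absolute 15-point margin, equal true success in both arms and all 36 patients per arm evaluable. This merits correction, but it does not show that the trial is unsound or that its conclusion is open to choice in most outcomes.

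**What to change.** Before outcome data are seen, state one decision rule in both the Sample size calculation and Statistical analysis sections:

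- the one-sided alpha with its matching interval: 0.025 with a two-sided 95% CI, or 0.05 with a 90% CI;
- the interval method, for example Newcombe or Wald;
- the limit: vNOTES is non-inferior on completion with the allocated technique if the lower limit for vNOTES minus TU-LESS lies above −15 percentage points.

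State in the Statistical analysis section that p < 0.05 is two-sided and applies to the other comparisons.

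Replace the 85% with the power at the chosen alpha and method. By normal approximation this is 81% (5%) or 72% (2.5%) at 54 evaluable, and 90% or 83% at 72. With Newcombe limits at 72 it is about 79% or 65%.

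The cost is a sentence or two in each section and no extra patients. The stated power becomes less favourable at 54 evaluable, and at 72 under most of these choices. If the sponsor wants to keep 85% as a target by normal approximation, 62 or 76 evaluable patients are needed at 5% or 2.5%.

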## Abbreviations

BIQ: Body Image Questionnaire
BMI: Body mass index
CC: Cohort Coordinator
CM: Cohort Manager
CT: Computer Tomography
CWCCH: Chengdu Women’s and Children’s Central Hospital
FSFI: Female Sexual Function Index
GEE: Generalized estimating equations
HALON: Hysterectomy by transabdominal laparoscopy or natural orifice transluminal endoscopic surgery
HIS: Hospital Information System
IH: Incisional Hernia
MIS: Minimally Invasive Surgery
MPL: Multiport Laparoscopic Surgery
MRI: Magnetic Resonance Imaging
NOTABLE: Transvaginal natural orifice transluminal endoscopic surgery (vNOTES) adnexectomy for benign pathology compared with laparoscopic excision
OA: Outcome Assessors
PDQ: Pregnancy and Delivery Questionnaire
PROMs: Patient Reported Outcome Measures
RCT: Randomized Control Rial
TU-LESS: Transumbilical Laparoscopic Single Site Surgery
VAS: Visual Analog Scale
vNOTES: Transvaginal Natural Orifice Transluminal Endoscopic Surgery
vNOTESTEP: Transvaginal Natural Orifice Transluminal Endoscopic Surgery in Treating Ectopic Pregnancy cohort study

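### The sample size gives TU-LESS the same 95% success as vNOTES, using vNOTES rates only, although the Background reports slightly more conversions with vNOTES; the zero difference behind the 85% power is not justified, with a modest effect

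*Protocol article*

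**What the plan says.** All of the sizing is in the Protocol article, under Sample size calculation.

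- **Design:** "A one-sided non-inferiority test was used to determine the sample size". The margin is 15 percentage points, described as vNOTES remaining preferable "despite a potential 15% lower success rate compared to TU-LESS".
- **Planning rates:** "To achieve 85% power for non-inferiority with a 95% expected success rate in both groups, a total of 54 cases were required". The total then becomes 72, or 36 per arm, after an allowance for dropout.
- **Source of the 95%:** "Previous studies report a conversion rate for vNOTES in tubal ectopic pregnancies between 1.83% and 3.07%, suggesting a surgical success rate of approximately 95" per cent. These are vNOTES figures.
- **Other stated basis:** "Sample size estimation was based on the NOTABLE cohort study". No rate is quoted from that study. The Abbreviations expand its name as "Transvaginal natural orifice transluminal endoscopic surgery (vNOTES) adnexectomy for benign pathology compared with laparoscopic excision", so TU-LESS is not named as its comparator.

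The Background says of retrospective studies that "vNOTES has lower perioperative complication rates but slightly higher conversion rates than TU-LESS". Reference 34 is cited there and again for the vNOTES rates in the sample size paragraph.

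The sized endpoint is the primary short-term outcome, finishing the operation by the assigned route. Conversion is its complement.

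**The concern.** Non-inferiority power depends directly on the assumed true difference. Equal rates are a natural default when no difference is expected. Here the document reports an expected difference on the sized endpoint, in the direction that uses up margin, and then plans as if there were none without saying why. The control arm's rate is borrowed from the experimental arm.

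What is at stake is how the result will be read. If the chance of a conclusive result is lower than stated, an inconclusive trial could be taken as evidence against vNOTES when it mainly reflects limited information.

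**Working it through.** **Inputs.** From the sample size paragraph: 95% success in both arms, margin m = 0.15, one-sided test, 54 evaluable (27 per arm), 72 enrolled (36 per arm). Cited vNOTES conversion of 1.83% to 3.07% means success of 100 − 3.07 = 96.93% to 100 − 1.83 = 98.17%.

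**Assumptions.** The article gives no TU-LESS rate, so a range is used. It gives no alpha for the non-inferiority test. One-sided 5% is used here, with 2.5% where noted. It names no test, so two are shown.

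**Step 1: the plan's own figure.** With δ the TU-LESS rate minus the vNOTES rate, the unpooled normal formula is

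power = Φ[(m − δ)/SE − z₁₋α], SE = √{[p_V(1 − p_V) + p_T(1 − p_T)]/n}.

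At 95% in both arms and n = 27: SE = √(0.095/27) = 0.0593; 0.15/0.0593 = 2.529; 2.529 − 1.645 = 0.884; power = 81.2%. At one-sided 2.5% it is 71.5%.

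Solving for n per arm at one-sided 5%:
- 85% power: (1.645 + 1.036)² × 0.095/0.0225 = 30.4, so 31 per arm, 62 in total.
- 80% power: (1.645 + 0.842)² × 0.095/0.0225 = 26.1, so 27 per arm, 54 in total.

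So 54 matches 80% power with this formula, not 85%. That is a separate fault and is not counted in the losses below.

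**Step 2: a small TU-LESS advantage, vNOTES at 95%.** Example with TU-LESS 97%, n = 27: SE = √[(0.0475 + 0.0291)/27] = 0.0533; (0.15 − 0.02)/0.0533 = 2.441; 2.441 − 1.645 = 0.796; power = 78.7%.

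The score-test column sums exact binomial probabilities over all outcome pairs for the Farrington–Manning test (attained size about 5.2% to 5.5%).

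| n per arm | TU-LESS | Unpooled formula | Score test, exact |
|---|---|---|---|
| 27 | 95% | 81.2% | 61.8% |
| 27 | 96% | 79.9% | 56.2% |
| 27 | 97% | 78.7% | 49.8% |
| 36 | 95% | 89.9% | 78.6% |
| 36 | 96% | 88.9% | 74.3% |
| 36 | 97% | 88.0% | 69.0% |

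Loss against equal rates, for differences of 1 and 2 points:
- Unpooled formula: 1.3 and 2.5 points (27 per arm); 1.0 and 1.9 points (36 per arm).
- Score test: 5.6 and 12.0 points (27 per arm); 4.3 and 9.6 points (36 per arm).

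The unpooled loss is small because a higher TU-LESS rate also shrinks the variance. At one-sided 2.5% with 36 per arm, the unpooled figures are 83.1%, 81.8% and 80.5%.

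**Step 3: the cited vNOTES rates instead of the rounded 95%.** One-sided 5%:

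| vNOTES / TU-LESS | Unpooled, 27 | Score, 27 | Unpooled, 36 | Score, 36 |
|---|---|---|---|---|
| 95% / 95% (as planned) | 81.2% | 61.8% | 89.9% | 78.6% |
| 96.93% / 98% | 94.7% | 60.1% | 98.3% | 81.5% |
| 96.93% / 99% | 95.8% | 52.3% | 98.8% | 76.3% |
| 98.17% / 99% | 99.7% | 68.2% | 100.0% | 89.5% |

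With the unpooled formula, every scenario beats the planned one. With the score test, power lies on either side of it.

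**The case against.** The strongest reply has four parts.

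1. Equal true rates are a common non-inferiority convention, and the Background evidence is retrospective and says only "slightly". This stands as a reason for moderation. It does not supply the missing justification, because the convention suits the case where no difference is expected.

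2. Planning at 95% when the cited vNOTES success is 96.9% to 98.2% is already conservative. This largely stands, as Step 3 shows. But the protocol does not offer it as its reason, and with the score test the cushion does not always cover the gap (52.3% against 61.8% at 27 per arm).

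3. The endpoint is known at the end of the operation, so long-term dropout should hardly reduce it and 36 per arm is the more realistic case. This is reasonable, and is why both sizes are shown.

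4. An article may leave fuller justification to the full protocol. That is true of detail. It does not remove a planning assumption that conflicts, as printed, with the article's own Background.

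A reader might infer something stronger: that the equal-rates assumption costs 10 to 28 points and leaves the trial badly underpowered. Score-test power does fall to 34.2% at 27 per arm, and 54.9% at 36 per arm, if vNOTES stays at 95% and TU-LESS is 99%. But that keeps the conservative rounding for one arm and removes it for the other. At the cited vNOTES rates the gap cannot exceed 3.07 points even if TU-LESS never converts. The drop from 85% to 62% at equal rates likewise reflects the choice of test and the mismatch in Step 1, not the zero difference. Putting the gap below 95% instead (vNOTES 94% or 93%, TU-LESS 95%) gives unpooled power of 73.0% or 64.4% at 27 per arm, but needs about twice the highest cited vNOTES conversion rate or more.

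**Conclusion.** The point holds in a limited form. The zero planning difference is unsupported: the 95% rests on vNOTES data only, no TU-LESS rate is given, and the Background reports a small difference against vNOTES on the sized endpoint.

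The size is modest: about 1 to 2.5 points of power with the unpooled formula and about 4 to 12 points with the exact score test. This assumes vNOTES at 95%, TU-LESS 1 to 2 points higher and one-sided 5%. The rounding down to 95% offsets part or all of it. The documents do not show that the trial is seriously underpowered for this reason, nor that more patients are needed.

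The stated 85% still needs restating. At the planned rates, 54 patients give at most about 81% under the two methods shown at one-sided 5%, and less with any TU-LESS advantage at 95% vNOTES success. With all 72 evaluable, the unpooled formula clears 85% at one-sided 5% (88.0% to 89.9%), but the score test does not (69.0% to 78.6%).

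**What to change.** In the Protocol article, Sample size calculation:

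- State separate success rates for vNOTES and TU-LESS with their sources. The comparisons already cited in the Background are the obvious place to look for the TU-LESS figure. Alternatively, keep equal rates and say explicitly that 95% is a deliberately conservative choice, and why a zero difference is acceptable given the Background.
- State the one-sided alpha and the non-inferiority test.
- Replace the single 85% with the recomputed power of the existing 72 patients, at 27 and 36 evaluable per arm, over a short range of small differences. Drop the 85% claim where it is not met.

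Keep enrolment at 72. The cost is one recalculation and a reworded paragraph, with no extra patients. The downside is a stated power that may be less favourable.
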